## Abstract

**Background:**

Due to an increase in PTSD patients seeking help in the Danish mental health sector and the addition of Complex PTSD to the ICD-11, there is a need to increase efficiency of existing treatments for PTSD. mHealth interventions have been shown to reduce PTSD symptoms. Therefore, the implementation of a mHealth intervention designed for psychiatric PTSD patients as a therapy add-on may improve treatment outcome. No study to date has explored the effects of mHealth interventions for PTSD in the Danish mental health sector, the feasibility and effect of this type of intervention needs testing.

**Methods:**

The study is an investigator-initiated randomized controlled feasibility trial investigating the clinical mHealth tool *PTSD help* combined with care as usual (CAU) compared to CAU for adults with PTSD. Seventy patients will be recruited and receive either the mHealth intervention combined with CAU or CAU alone. The primary feasibility outcome is the proportion of eligible patients that participate in the study until the end assessment. Secondary outcome data consists of the fraction of compliant patients in the experimental group and exploratory data on *PTSD help* on PTSD symptom severity, level of psychological distress, sleep quality, dissociation symptoms, therapy readiness, quality of life, disability levels, and recovery.

**Discussion:**

This study may help increase our knowledge of possible benefits of, as well as potential barriers to, the implementation of mHealth tools in the psychiatric sector. It may also provide a cost-efficient means to increase therapy outcomes and decrease the duration of suffering for PTSD patients in the psychiatric sector.

**Trial registration:**

The trial is registered at ClinicalTrials.gov (ID: NCT03862703) https://clinicaltrials.gov/ct2/show/NCT03862703 on the 27 of February 2019 and has been approved by the Danish Data Protection Agency (journal number: VD-2018-200 ISuite number 6443). Referring to the committee law §2, the National Committee on Health Research Ethics (DNVK) [H-18024180] decided that the study could proceed without approval as the use of *PTSD help* did not constitute a health science intervention according to Danish health science legislation.

## Background

Post-traumatic stress disorder (PTSD) is a potentially disabling and often protracted psychiatric disorder, which may develop as a response to one or several severely traumatic events. The prevalence of PTSD depends on several factors (e.g., the diagnostic system and assessment procedures), but across a range of European countries, the lifetime prevalence of PTSD is estimated to be approximately 2% [1]. The past years have seen a marked increase in the number of patients referred for PTSD treatment in Mental Health Services in the Capital Region of Denmark (MHS-CRD) from 453 in 2015 to 746 in 2017.

ICD-11 PTSD is comprised of three core symptoms: re-experiencing, avoidance, and hyperarousal (World Health Organization, 2018). In 2018, Complex PTSD (C-PTSD) was included in ICD-11 (World Health Organization, 2018). It contains the core PTSD components and an additional component reflecting “disturbances in self-organization” (DSO) comprised of affective dysregulation, negative self-concept, and disturbances in relationships [7, 18]. Furthermore, patients with C-PTSD are characterized by a higher frequency of childhood traumatic experiences and greater functional impairment [32] in comparison to PTSD patients. Cloitre et al. [20] report that C-PTSD is a predictor of drop-out and poor treatment response in some of the current first-line treatments for PTSD, and it has been suggested that this patient group may benefit from stabilizing interventions prior to trauma-focused psychotherapy [8, 17, 20]. Thus, there is a need to develop new treatment approaches that include stabilizing interventions for patients with C-PTSD.

Over the last decade, psychiatric treatment providers across the world have developed mobile technology both as standalone treatments and as supplements to existing treatments for mental health problems [5, 24]. The use of mobile health tools (mHealth) in mental health care is argued to have several potential advantages: mHealth tools can be easily integrated in daily life [4], they can reach people that do not normally seek mental health treatment [46], they can assist patients in getting psychoeducation [35, 40], and they can be used to monitor symptoms [14, 15, 35]. In addition, mHealth tools have the potential to improve the cost-effectiveness of interventions through the optimization of the clinicians’ time and resources and improve treatment effect by improving therapy engagement and adherence [14, 16, 21, 23, 48].

Existing clinical evaluations of mHealth tools have found promising indications of their efficacy in reducing patients’ symptoms and general level of psychological distress [27, 38]. Clinical studies investigating mHealth tools used as a psychotherapy add-on have also found enhanced compliance with treatment [45, 47], and increased treatment outcome, both immediately after end of treatment, and at 6-month follow-up, which may be partially due to an increase in patient adherence to homework [10, 39]. However, more research is needed to substantiate these results as most studies to date have not been replicated or have had methodological limitations such as a lack of control groups or small sample sizes [23, 38, 39, 43].

So far, mHealth apps for PTSD patients have primarily been designed for use by American veterans with PTSD [34, 44]. To address the needs of non-veteran PTSD patients, we developed an mHealth app, *PTSD help* (Danish: *PTSD hjaelp*), designed to supplement psychotherapeutic treatment for PTSD across psychotherapeutic modalities and PTSD subgroups. *PTSD help* focuses on psychoeducation (about PTSD symptoms, diagnosis, triggers, epidemiology, treatment, prognosis, aetiology, and advice for next of kin), emotion-regulating tools (e.g., breathing exercises, grounding exercises, calming images, body exercises, sleep advice, and guided meditations), crisis management (e.g., crisis plan), and finally, self-monitoring of PTSD symptoms and sleep quality. To ensure the usability of *PTSD help* across treatment modalities, the app does not include specific treatment elements as these are delivered in face-to-face psychotherapeutic treatment.

We have found no studies of mHealth tools for PTSD in a Danish treatment context, which makes it difficult to ascertain possible roadblocks for the implementation of mHealth tools in a Danish psychiatric context. However, a relatively broad implementation seems to be practically possible, as more than 85% of all Danes between 15 and 75 years own a smartphone. Because *PTSD help* is an untested clinical mHealth tool, it is necessary to test if it is possible to successfully recruit patient for an RCT testing efficacy of *PTSD help*, a Danish psychiatric context.

We therefore plan to conduct a feasibility study with the primary aim of ascertaining feasibility of randomization and investigate levels of patient compliance before conducting a larger randomized controlled trial (RCT) on treatment efficacy. The primary objective for the present study is to assess the feasibility of using *PTSD help* in the MHS-CRD to inform a larger future RCT study. The secondary objective is to gather preliminary exploratory data on the effectiveness of *PTSD help* versus treatment as usual on a range of clinically relevant outcome variables, including exploring C-PTSD as a potential moderator of subgroup-specific effects.

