## Methods

The study is an investigator-initiated randomized controlled feasibility trial investigating *PTSD help* combined with care as usual (CAU) compared to CAU for adults with PTSD. The primary feasibility outcome is the proportion of eligible patients that participates in the primary app intervention before entering psychotherapy and provide data at the T1 (baseline) and T2 (post-app intervention) assessment. The secondary feasibility outcome is the fraction of compliant patients in the experimental group, and additional explorative outcome data consists of PTSD symptom severity, level of psychological distress, sleep quality, dissociation symptoms, therapy readiness, quality of life, negative events, and user satisfaction. This data will be collected using electronic questionnaires administered via participants email.

The primary outcome will be assessed at T2 6 weeks after randomization. The secondary feasibility outcome will be assessed continuously by logging the patient’s interactions with the application. Secondary outcomes will be assessed prior to randomization and start of *PTSD help* intervention (T1), at post-primary *PTSD help* intervention (T2) and at the end of psychotherapeutic treatment (T3). The design of this trial has been developed with attention to the criteria outlined in the SPIRIT 2013 guidelines [13] (see Fig. 1 for a consort diagram).

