### Feasibility outcome

The primary feasibility outcome is the proportion of eligible patients that agree to be randomized and participate in assessment 1 (T1, week 1) and 2 (T2, week 7). The secondary feasibility outcome is the fraction of compliant patients in the experimental group that is patients that actively use the system after. Compliance is defined as the use of *PTSD help* functions (excluding self-monitoring tools) corresponding to use twice a week (mean), assessed over 6 weeks pre-treatment, and during the psychotherapy treatment period. Compliance data is collected from the tracking log of the patient’s app activity through a secured webpage. In addition, compliance will be assessed through a *user behaviour questionnaire,* an 11-item questionnaire developed by the project group for the current study by selecting and modifying relevant items from questionnaires used in earlier studies evaluating the *PTSD Coach* app [34, 44] (see Additional file 1).

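### The primary aim and objective include app use and compliance, but the detailed primary outcome measures only randomisation and retention, and the article words that outcome inconsistently

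*Protocol article*

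**What the plan says.** **Aim and objective (Background, last paragraph).** The study has a "primary aim of ascertaining feasibility of randomization and investigate levels of patient compliance". The next sentence reads "The primary objective for the present study is to assess the feasibility of using" PTSD help in the regional mental health services, to inform a larger trial. The secondary objective concerns effectiveness only, so compliance stands at the primary level.

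**Primary outcome.** The article words it in several ways:

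- Feasibility outcome: the "proportion of eligible patients that agree to be randomized and participate in assessment 1" (T1) and assessment 2 (T2).
- Methods, opening paragraph: "the proportion of eligible patients that participates in the primary app intervention before entering psychotherapy and provide data at the T1 (baseline") and at T2.
- Abstract, Methods: "The primary feasibility outcome is the proportion of eligible patients that participate in the study until the end assessment".
- Statistical analysis: primary and secondary outcomes are described together, with T2 attendance, average system use and retention to the end of the study as examples.

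**Compliance (Feasibility outcome).** "The secondary feasibility outcome is the fraction of compliant patients in the experimental group". It is defined as mean use of twice a week, self-monitoring tools excluded, over the six pre-treatment weeks and during psychotherapy. It is taken from the app log, with a user behaviour questionnaire in addition.

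**Design and precision.** Allocation is 1:1 (Randomization), and only the experimental group receives the app (Procedure). Sample size plans 70 patients and gives a 95% interval of 0.38 to 0.62 at an observed proportion of 0.50, naming compliance as its example.

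**The concern.** The primary outcome should be able to answer the primary objective. Here the objective concerns use of the app and the aim names compliance, yet the detailed primary outcome has no element of use. T2 is a set of questionnaires reached through an emailed link, so a patient can complete it without opening the app. About half of those counted are controls who are never given it.

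The Methods opening does bring in the app, but it conflicts with the detailed definition and does not say what participating means. Two analysts following the two sections could report different headline percentages from the same data.

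What is at stake is the conclusion. Statistical analysis says an efficacy trial will follow if the results indicate feasibility, without saying how the two feasibility outcomes combine. Good retention alongside poor use would leave the stated objective unanswered by the outcome labelled primary.

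**Working it through.** **Inputs.** 70 patients (Sample size); 1:1 allocation, so about 35 per arm (Randomization); app in the experimental arm only (Procedure); outcome definitions as set out above. The article gives no number of eligible patients, so E is an assumption and is varied.

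**Step 1: reproduce the plan's interval.** Formula: p ± 1.96 × √(p(1 − p)/n). With p = 0.50 and n = 70:

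- standard error = √(0.25/70) = 0.0598; half-width = 1.96 × 0.0598 = 0.117
- interval 0.383 to 0.617; the exact (Clopper-Pearson) interval is 0.378 to 0.622

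Both round to the stated 0.38 to 0.62. The figure is right for a proportion among 70 patients.

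**Step 2: the same interval for compliance as defined.** Compliance exists only in the experimental arm, so n is about 35:

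- standard error = √(0.25/35) = 0.0845; half-width = 1.96 × 0.0845 = 0.166
- interval 0.334 to 0.666; Wilson 0.343 to 0.657; exact 0.327 to 0.673

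The interval for compliance is therefore about 0.33 to 0.67.

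**Step 3: does the detailed primary outcome depend on app use?** Let A and C be the numbers of app and control patients who agree to randomisation and take part in T1 and T2. The outcome is (A + C)/E. The number of app users does not appear in it. If all 70 take part in both assessments, the value is 70/E whether 0 of 35 or 35 of 35 use the app, and 35 of the 70 counted (half) are controls without access.

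**Step 4: the Methods wording.** Read literally, a control cannot take part in the app intervention, so the largest numerator is 35. Best attainable values, with 70 randomised and all providing T1 and T2 data:

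| Assumed eligible E | Feasibility outcome wording, 70/E | Methods opening, literal, 35/E |
|---|---|---|
| 70 | 100% | 50% |
| 100 | 70% | 35% |
| 140 | 50% | 25% |

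The ratio is 2 for any E. If participating is instead read loosely, as being in the study during the app period, controls count again and the wording loses its app-use element.

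**Step 5: illustration (assumed, not in the article).** Suppose all 70 take part in T1 and T2 and 7 of 35 app patients are compliant: 7/35 = 20%, exact 95% interval 8% to 37%. The detailed primary outcome stays at its maximum of 70/E. Refusals before randomisation still lower it through E; lack of use does not.

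**The case against.** The strongest reply is that this is a feasibility study for a later trial. The Background says it must be tested whether patients can be recruited for an efficacy trial, the aim puts randomisation first, and the Discussion describes the purpose as the feasibility of a large-scale trial. For that purpose, acceptance of randomisation and retention to T2 in both arms is a direct measure, and counting controls is right. This stands: the primary outcome does answer the randomisation and retention half of the aim.

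Three stronger readings are tempting, and the article does not support them.

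- *The primary outcome nowhere involves the app.* The Methods opening includes participation in the app intervention. The absence of use holds for the Feasibility outcome and Abstract wordings and for the T2-attendance example in Statistical analysis.
- *App use is hardly measured.* It is covered by the log, the user behaviour questionnaire and average usage, with app dropout and user satisfaction as exploratory outcomes. The issue is rank and the link to the conclusion.
- *A good primary result alone triggers the efficacy trial.* Statistical analysis treats primary and secondary outcomes together and descriptively and ties the decision to neither alone. The Discussion says app-use patterns will inform the next trial. The article states no threshold, so the primary outcome cannot be said to be met or failed.

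With no test and no threshold, the primary label has limited inferential force. It still determines which result is read as the answer to the primary objective, and the mismatch with the Background remains.

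**Conclusion.** The point holds in a limited form. The primary aim and objective cover compliance and use of the app, while the detailed primary outcome covers agreement to randomisation and retention only. By definition that outcome is unaffected by whether 0 or all of about 35 app patients use the app. In practice use and T2 response may be correlated, but nothing in the definition requires it.

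The primary outcome is also inconsistently worded. Between the Feasibility outcome section and a literal reading of the Methods opening, the best attainable value differs by a factor of 2, assuming 35 per arm and full T1 and T2 participation. The Abstract's end assessment is not tied to T2.

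The interval under Sample size is correct for 70 patients but too narrow for compliance, which at 0.50 has about 0.33 to 0.67 on about 35 patients.

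The data needed to answer the objective are already planned. What needs correcting is the definition, the ranking and the rule for concluding feasibility.

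**What to change.** 1. Use one definition in the Abstract, the Methods opening, Feasibility outcome and Statistical analysis, with two co-primary feasibility outcomes: (a) the proportion of eligible patients who agree to randomisation and complete T1 and T2, both arms; (b) the log-based compliant fraction in the app arm over the six pre-treatment weeks.
2. State in Statistical analysis that feasibility is concluded only if both are judged adequate, and report each with its own denominator and 95% interval: eligible patients for (a), about 35 app patients for (b). No multiplicity correction is needed, since both are descriptive and both are required.
3. In Sample size, give compliance its own interval, about 0.33 to 0.67 at 0.50, and do not use compliance as the example for 70 patients.

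If the sponsor prefers recruitment and retention as the sole primary outcome, reword the aim and objective in the Background to match and keep compliance secondary. The definition must still be made uniform and the compliance interval corrected.

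**Cost.** Changes of wording and a registry update; the log data are already collected. Under the co-primary option feasibility becomes harder to claim, and (b) is less precise than the plan now suggests.

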## Methods

The study is an investigator-initiated randomized controlled feasibility trial investigating *PTSD help* combined with care as usual (CAU) compared to CAU for adults with PTSD. The primary feasibility outcome is the proportion of eligible patients that participates in the primary app intervention before entering psychotherapy and provide data at the T1 (baseline) and T2 (post-app intervention) assessment. The secondary feasibility outcome is the fraction of compliant patients in the experimental group, and additional explorative outcome data consists of PTSD symptom severity, level of psychological distress, sleep quality, dissociation symptoms, therapy readiness, quality of life, negative events, and user satisfaction. This data will be collected using electronic questionnaires administered via participants email.

The primary outcome will be assessed at T2 6 weeks after randomization. The secondary feasibility outcome will be assessed continuously by logging the patient’s interactions with the application. Secondary outcomes will be assessed prior to randomization and start of *PTSD help* intervention (T1), at post-primary *PTSD help* intervention (T2) and at the end of psychotherapeutic treatment (T3). The design of this trial has been developed with attention to the criteria outlined in the SPIRIT 2013 guidelines [13] (see Fig. 1 for a consort diagram).

**Fig. 1 Fig1:**
[figure not shown]
Consort diagram

The trial is registered at ClinicalTrials.gov (ID: NCT03862703) and has been reviewed by the Danish Data Protection Agency (journal number: VD-2018-200 ISuite number 6443). Referring to the committee law §2, the National Committee on Health Research Ethics (DNVK) [H-18024180] decided that the study could proceed without approval as the use of *PTSD help* did not constitute a health science intervention according to Danish health science legislation.

### Participants

The study will recruit patients referred with PTSD symptoms to the Centre for Visitation and Diagnostics (CVD) under the MHS-CRD, with the following inclusion criteria: the patient (1) must be at least 18 years old, (2) fulfil the DSM-5 PTSD diagnosis criteria, (3) be referred to PTSD care package treatment [22], (4) have access to a smartphone with iOS (Version 10 or higher) or Android (Version 5.0.1 or higher), and (5) provide informed consent. Exclusion criteria are patients with (1) suicidal risk, (2) ongoing episode of bipolar disease or psychotic disorder, (3) current abuse of alcohol or drugs, (4) inability to understand and/or read Danish, and (5) concurrent psychiatric or psychological treatment of PTSD outside of MHS-CRD.

### Randomization

Randomization is conducted through the data management software REDCap, which allows a setup where no one from the research team has knowledge of or access to the underlying computer-generated allocation sequence. The randomization uses permuted blocks with varying block sizes based on a computer-generated allocation sequence created by a researcher with no affiliation to the project. The randomization allocation ratio is 1:1. This procedure ensures that researchers are blinded to the allocation process as the randomization allocation list, and block size is unknown to the researchers. The randomization procedure will be stratified by presence of Complex PTSD as measured with the International Trauma Questionnaire [18].

### Blinding

Patients will be randomized after baseline assessment to ensure assessors and patients are blinded during the assessment. All assessments post-randomization will consist solely of self-report measures administered via email through REDCap and logging of user activity in the app.

### Procedure

Patients referred to CVD for diagnostic screening that are diagnosed with PTSD and accepted for PTSD outpatient treatment in MHS-CRD will be invited to participate in the study by the clinician conducting the screening. The invitation will include a leaflet with information about the study and contact information for the project. If the patient gives their consent for participation, he or she will be booked for an assessment interview. Patients who provide written consent and complete the assessment interview will be randomized if they fulfill the inclusion/exclusion criteria. After randomization, patients in the experimental group will be given immediate access to *PTSD help.* After 3 days, they will receive a phone call to ascertain whether they are experiencing any technical difficulties using the app. The second and third assessments will be administered electronically via a link to the questionnaires sent in an email through REDCap (see Fig. 1 for a consort diagram).

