### Statistical analysis

The primary and secondary outcomes are analyzed through descriptive statistics, e.g., percentage of patients that show up at T2, the average usage of the system over the intervention period, and the proportion of patients that stay in study until the end.

Analysis of between-group effects on explorative outcome measures will be analyzed with analysis of covariance, using the intervention arm as the main predictor and baseline severity and the stratification variable from randomization as covariates. For binary outcomes (e.g., compliance), logistic regression will be used. Due to the exploratory nature of this feasibility study, missing data will not be imputed but the amount of missingness will be reported. Results will be presented as covariate adjusted group differences or odds ratios, along with the 95% confidence interval. If the results indicate feasibility, we will proceed to a randomized controlled efficacy study.

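### The primary outcome counts eligible patients who agree to randomisation, but consent is itself an inclusion criterion and the full criteria are settled only after consent, so eligible decliners cannot be identified

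*Protocol article*

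**What the plan says.** All three statements of the primary outcome in the protocol article use eligible patients as the denominator:

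- Abstract, Methods: "The primary feasibility outcome is the proportion of eligible patients that participate in the study until the end assessment".
- Methods, opening paragraph: "The primary feasibility outcome is the proportion of eligible patients that participates in the primary app intervention before entering psychotherapy", with data at T1 and T2.
- Feasibility outcome: "The primary feasibility outcome is the proportion of eligible patients that agree to be randomized and participate in assessment 1", and in assessment 2 at week 7.

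The Participants section numbers consent among the inclusion criteria: "5) provide informed consent".

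The Procedure section gives the order of events. Patients "diagnosed with PTSD and accepted for PTSD outpatient treatment in MHS-CRD will be invited to participate in the study" by the screening clinician. Those who consent are booked for an assessment interview. Then: "Patients who provide written consent and complete the assessment interview will be randomized if they fulfill the inclusion/exclusion criteria". The Assessment interview section places the structured diagnostic interview (MINI), which supplies the study's DSM-5 PTSD diagnosis and the comorbidity check, at that appointment.

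The Statistical analysis section says the primary and secondary outcomes are described with descriptive statistics and gives examples, the first being "percentage of patients that show up at T2". It names no denominator.

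**The concern.** A proportion who agree to randomisation carries information only if people who could have agreed and did not are in the denominator. With consent inside the definition of eligibility, a refusal removes the patient from the denominator instead of lowering the proportion. Setting the consent criterion aside does not fully solve this, because the study's own diagnosis and comorbidity check are never made for a patient who declines before the interview.

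This touches the trial's main purpose. The Background says the trial must test whether patients can be recruited for an efficacy RCT, and it names feasibility of randomisation as the primary aim. The Discussion intends to use the results to improve recruitment, and the Statistical analysis section makes the efficacy trial depend on whether the results indicate feasibility. If retention among consenters were reported as uptake among eligible patients, recruitability would be overstated and the next trial's recruitment plan would rest on the wrong figure.

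**Working it through.** **The plan's own figure.** The Sample size section gives a 95% interval of 0.38 to 0.62 for an observed proportion of 0.50 with 70 patients. The Wald formula p ± 1.96 × √(p(1 − p)/n) gives 0.50 ± 1.96 × √(0.25/70) = 0.50 ± 0.117, that is 0.383 to 0.617. The figure reproduces. It is stated for a proportion among the 70 recruited patients and is not itself affected by this point.

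**What the definitions imply, component by component**

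| Component of the primary outcome | Can it fail for a patient classed as eligible under Participants and Procedure? |
|---|---|
| Agrees to be randomised | No. Consent is an inclusion criterion, and consenting, interviewed patients who meet the criteria are randomised. |
| Takes part in T1 | No. The Blinding section puts randomisation after the baseline assessment. |
| Takes part in T2 | Yes. Dropout after randomisation lowers the result. |

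On the literal reading, only T2 attendance can vary.

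**How much the denominator matters.** The documents give neither an uptake rate nor a T2 completion rate, so both are assumptions here.

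- n = 70 randomised (Sample size section).
- r = 0.80, assumed T2 completion, so 0.80 × 70 = 56 patients reach T2.
- u = assumed share of invited patients who agree: 30%, 50% or 70%.
- Every consenter is assumed to pass the interview, so the number invited is N = 70/u.
- Primary proportion counting decliners = 56/N = u × r.
- 95% intervals by Wilson: [p + z²/(2N) ± z√(p(1 − p)/N + z²/(4N²))] / (1 + z²/N), with z = 1.96.

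| Denominator | N | Proportion | 95% CI |
|---|---|---|---|
| Literal (consenters only), any uptake | 70 | 56/70 = 80% | 0.69 to 0.88 |
| Invited, 70% agree | 70/0.7 = 100 | 56/100 = 56% | 0.46 to 0.65 |
| Invited, 50% agree | 70/0.5 = 140 | 56/140 = 40% | 0.32 to 0.48 |
| Invited, 30% agree | 70/0.3 ≈ 233 | 56/233 = 24% | 0.19 to 0.30 |

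**Sensitivity to T2 completion.** At 50% agreement, completion of 70% gives 0.5 × 0.7 = 35% against a literal 70%. Completion of 90% gives 0.5 × 0.9 = 45% against a literal 90%. The ratio of the two results is always u.

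**Sensitivity to the interview.** If only a share e of consenters pass, the figure over all invited patients is u × e × r. That is lower still, and it then mixes ineligibility with refusal. This is why the steps need to be reported separately.

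**The case against.** The strongest reply is that the literal reading is not the natural one. A phrase about eligible patients agreeing to be randomised makes sense only if some eligible patients do not agree, so the authors probably meant eligible apart from consent. This stands. A reader might infer that the outcome is circular beyond doubt, and the documents do not support that. They show an outcome definition that conflicts with the criteria and the procedure. The reply does not remove the conflict, because the intended reading needs a count of eligible decliners and the described sequence does not produce one.

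Three further limits also stand:

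- A reader might infer that nothing about eligibility is known before consent. In fact the clinical PTSD diagnosis and acceptance for outpatient treatment both precede the invitation. What waits until after consent is the study's DSM-5 diagnosis and the application of the full criteria.
- A reader might take the Statistical analysis section as proof that only T2 attendance will be computed. It is a list of examples covering primary and secondary outcomes together. It is compatible with the literal reading and does not establish it.
- The CONSORT diagram is not shown and may count refusals, and screening logs are often left to a full protocol. The absence of a described log is therefore not the complaint. A count of refusals in a flow chart would still leave open which denominator defines the primary outcome.

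Finally, replacing eligible with invited patients counts some people who would have failed the interview as recruitment failures. The Participants section has several exclusions that could produce such failures, and their frequency is unknown. This is a real cost of the fix and is dealt with there.

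**Conclusion.** The point holds as an internal conflict. The Feasibility outcome section needs decliners in the denominator. The Participants section defines them out, and the Procedure and Assessment interview sections settle the full criteria too late to identify those who were otherwise eligible. Followed literally, the plan yields T2 retention among consenters, which does not measure the recruitability that the Background says must be tested.

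The size depends wholly on uptake, which the documents do not give. With 80% T2 completion among 70 randomised patients and all consenters passing the interview, the literal result is 80%, against 24% to 56% for uptake of 30% to 70%. With uptake near 100% the two results would agree. Refusal is the only loss that the literal definition hides; dropout between randomisation and T2 still lowers it.

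**What to change.** 1. State that, for the primary outcome, eligible does not include having consented.
2. Define the denominator as patients invited at screening who meet the criteria knowable before consent: PTSD diagnosed, accepted for MHS-CRD outpatient treatment, and any other criterion the screening clinician already knows.
3. Have the inviting clinicians keep an anonymous tally of invitations from the first day of recruitment, since decliners who are not counted at the time may not be recoverable.
4. Report the numbers invited, consented, interviewed, meeting criteria, randomised and assessed at T2. Give uptake and T2 retention as separate proportions, each with a 95% confidence interval.
5. Use this definition wherever the denominator of the primary outcome is stated: the Abstract, Methods and Feasibility outcome sections.

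The cost is a simple count by clinicians who already make the invitations, plus one clarifying definition. The overall figure will be lower, and because some invited patients would have failed the interview, it is a lower bound on the corresponding proportion among truly eligible patients. The step-by-step counts make that visible by showing how many of those interviewed failed the criteria.
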